## Abstract

**Background:**

Tobacco consumption is the most preventable cause of morbidity-mortality in the world. One aspect of smoking cessation that merits in-depth study is the use of an application designed for smartphones (app), as a supportive element that could assist younger smokers in their efforts to quit. To assess the efficacy of an intervention that includes the assistance of a smoking cessation smartphone application targeted to young people aged 18 to 30 years who are motivated to stop smoking.

**Discussion:**

To our knowledge this is the first randomised controlled trial of a programme comparing the efficacy of usual care with a smoking cessation intervention involving a mobile app. If effective, the modality could offer a universal public health management approach to this common health concern.

**Trial registration:**

NCT01734421

## Background

Tobacco consumption is the most preventable cause of morbidity-mortality in the world. Although the prevalence of tobacco use among adolescents and young adults in Europe has decreased in recent years, tobacco use continues to be a major health problem among young people with a lower educational level. According to, data from ESCA 2011, 30.6% of boys and 34.1% of girls, among 15–24 years smoke daily.

Many adolescent and young adult smokers want to stop smoking and report frequent attempts to quit [1]. Valdivieso et al. [2] recently reported high interest in smoking cessation (67%) among young people who were habitual smokers and who frequently expressed the difficulty of maintaining abstinence despite repeated attempts.

Primary health care has an essential role in smoking cessation. Results of a randomized clinical trial in Spain indicate that a smoking cessation intervention was effective in the adult population, with 8.1% of the intervention group participants reporting continued abstinence at one year, compared to 5.8% in the control group (p<0.014) [3].

However, no studies to date assessed the effectiveness of a structured smoking cessation intervention directed at young people. One aspect of smoking cessation that merits in-depth study is the potential usefulness of new technologies, in particular the use of an application designed for smartphones (app), as a supportive element that could assist younger smokers in their efforts to quit. New technologies –and specifically a targeted app-- offer three benefits that can be useful for this purpose: First, they reach people “where they are”, i.e. there is no need to go to any specific place to receive support services. Second, they promote interactivity, opening new channels of communication between patients and “experts”. And third, they provide instant access to information and assistance. Therefore, it seems logical to hypothesize that a smartphone app will be a useful tool to offer additional support when a young adult wants to stop smoking [4].

Some efforts have already been made in this direction. Clinical trials have evaluated the effectiveness of smoking cessation interventions in adolescents and young people that made use of text messages (SMS), with significantly better results than in the control group (9% vs. 4% abstinence) [5,6]. A recent review by Cochrane [7] of the effectiveness of smoking cessation interventions that use mobile telephones concludes that further studies are needed to determine whether these technologies will assist in smoking cessation efforts. Of particular interest for clinical practice, a programme of text messages sent to mobile phones was effective in the short term (six weeks) and a combined programme of Internet and mobile phone messages up to 12 months.

According to a study by Fundación Telefónica (the foundation associated with Spain’s national telephone company), the number of “smartphones” (mobile phones with an advanced operating system such as Android or iOS) sold in the second trimester of 2011 exceeded for the first time the number of personal computers sold (107 million smartphones, compared to 85 million personal computers). In 2009, more than two thirds of the world’s population had mobile phone access and more than 4.2 billion text messages were sent [4]. We would point out that the youngest segment of the population is most likely to include new technologies in their everyday lives. This behaviour pattern is repeated in patterns of Internet access using mobile phones and 3G technologies, reaching 26% market penetration among young people in Spain --more than twice the European average for this population [4].

Parallel to the growth of smartphone devices, a series of apps have been developed with the objective of providing information and support concerning social and medical problems [8]. The world market for medical apps for smartphones and tablets multiplied seven-fold in 2011 alone, reaching a total of US$718 million, according to a market analysis by the American firm *research2guidance*[9]. At present, these apps are being used as instruments of patient education and support and are also helpful to healthcare professionals [10].

Nonetheless, the market for health care apps is very fragmented; many are designed for very specific contexts or low-incidence diseases. To our knowledge, no randomized studies have assessed the effectiveness of smoking cessation attempts in young people motivated to stop smoking using a smartphone app.

The objective of the present study is to evaluate the efficacy of an intervention that incorporates a smartphone app specifically designed to reduce the prevalence of tobacco consumption in motivated young adults aged 18 to 30 years.

## Methods

### Study design

This project will be developed in two phases, first the design and development of the specific app, followed by a randomized, clustered clinical trial aimed at assessing the efficacy of the smartphone app. The unit of randomization will be the primary care centres of Catalonia, which will assess the effectiveness of the app in achieving smoking cessation among motivated young smokers.

### Participants

#### Selection of participating primary care centres

Participation by primary care centres will be totally voluntary. At the beginning of the study a personalized letter will be sent to the attention of the centre administrators, requesting their collaboration and providing a copy of the study protocol. Within two weeks, the administrators will be contacted by telephone to confirm their participation. Each centre that agrees to participate will be randomized to the intervention or control group and a visit will be scheduled to inform the participating primary care physicians and nurses about the study.

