#### Randomisation

The unit of randomisation will be the primary care centre, stratified according to urban/rural location and number of participating professionals to ensure comparability between the study groups, and then assigned 1:1 to the intervention or control group. Randomisation will use the Epidat 3.0 programme.

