#### Blinding

Given the nature of the intervention, it is impossible to mask the participants or professionals to the study group assignments. However, data analysis will be blinded to any potential identifiers.

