### Intervention

During the recruitment period, or until the required quota of patients is reached, the family doctor and/or primary care nurse will invite patients aged 18 to 30 years who smoke 10 or more cigarettes per day to participate in the study. If the patient is eligible for inclusion and agrees to participate, informed consent will be requested (Figure 1). After signing informed consent, the participant’s demographic data will be collected and the study questionnaire will be administered (Fageström & Richmond). During this visit (visit 0) smokers with moderate motivation to stop smoking (Richmond score of 5–6) will be invited to schedule a second appointment to attempt to increase their motivation. For highly motivated participants (Richmond score of 7–10) a “quit day” will be established within the following 15 days (D-Day), and they will be invited to schedule an appointment for the day before their D-Day.

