## Discussion

The development of the proposed smartphone app, and subsequent evaluation of its effectiveness in our population, has the potential to contribute a useful tool for the smoking cessation efforts of young adults, as well as providing information about the effectiveness of smoking cessation interventions in a population that has not been studied in our environment.

A limitation of the study is its open character. Both patients and health care professionals will know that they are involved in the intervention, which might create a bias. The analysis will be blind, with no identifiers available to the statistician that would indicate whether a subject was assigned to the intervention or control group. The study will use random clustering of primary care centres to avoid the risk of contamination by taking geography into account.

The randomization process is intended to result in a balanced distribution of sociodemographic and cultural characteristics between intervention and control groups, both for doctors and nurses and for participating patients. To avoid contamination between the intervention and control groups, the game and the app itself will only be made available to the intervention group. Multivariate analysis will be used to control for possible confounding factors.

Another limitation is the difficulty of recruiting young patients who want to stop smoking. The multicentre study design, with 22 participating primary care centres and a long (18-month) recruitment period, is intended to ensure an adequate participant pool.

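### Centres are randomised before unmasked staff recruit patients, so patient balance at entry is not secured, and adjustment for baseline motivation and dependence is not guaranteed

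*Protocol article*

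**What the plan says.** The protocol article fixes this order of events.

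- **Allocation.** Under Selection of participating primary care centres: "Each centre that agrees to participate will be randomized to the intervention or control group and a visit will be scheduled to inform"; those informed are the doctors and nurses taking part. The caption of Figure 1 gives the same order, with centres randomised and patients then sampled.
- **Masking.** Under Blinding: "it is impossible to mask the participants or professionals to the study group assignments". Only the data analysis is blinded.
- **Recruitment.** Under Intervention: "the family doctor and/or primary care nurse will invite patients aged 18 to 30 years who smoke 10 or more cigarettes per day". The time limit on these invitations is worded as "During the recruitment period, or until the required quota of patients is reached". Consent, the Fagerström test and the Richmond test follow at visit 0. The app is first handed over at the appointment before D-Day.
- **Balance.** Under Randomisation, centres are "stratified according to urban/rural location and number of participating professionals to ensure comparability between the study groups". The Discussion adds: "The randomization process is intended to result in a balanced distribution of sociodemographic and cultural characteristics between intervention and control groups". It applies that aim to staff and patients alike: "both for doctors and nurses and for participating patients".
- **Adjustment.** Under Statistical analysis, baseline groups are compared, and covariates with p<0.30 in bivariate analyses enter the multi-level survival model. The Discussion says multivariate analysis will deal with possible confounding.

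The Discussion also concedes: "Both patients and health care professionals will know that they are involved in the intervention, which might create a bias".

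**The concern.** Randomising centres gives comparability of centres and their staff, within the limits of a trial with 22 centres. It extends to patients only if the route by which patients enter does not depend on the arm. Here the people who invite patients know their centre's arm, and so may the patients. A doctor with an app to offer may approach different smokers from a doctor offering usual care, and different smokers may accept.

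The eligibility criteria leave room for this. Every Richmond score from 5 to 10 qualifies, and the protocol itself separates moderate (5–6) from high (7–10) motivation. Motivation and dependence plausibly predict abstinence at 12 months, so a difference at entry would appear in the crude comparison of arms as a gain or a loss for the app. Blinding the statistician does nothing about who was enrolled.

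Adjustment is therefore the main analytic safeguard. As written, it does not guarantee that the two scores which best capture the likely difference will be in the model.

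**Working it through.** **1. Order of events.** Agreement → randomisation of the centre → visit to inform staff → invitation of patients by those staff. The selection section alone does not say that the arm is disclosed at that visit. Read with the statements that professionals cannot be masked and that they will know of their involvement, the recruiters are unmasked when they invite.

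**2. What each stated safeguard reaches.**

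| Safeguard | Reach |
|---|---|
| Stratification by location and number of professionals | Centre factors only |
| Same eligibility criteria in both arms | Limits the range of patients; Richmond 5–10 is still open |
| Blinded analysis | Does not affect who was recruited |
| Baseline comparison | Can show a measured imbalance; does not correct it |
| Multivariate adjustment | Measured covariates only, and only if bivariate p<0.30 |

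**3. The plan's own figures, used as the frame.** 2 × 222 × 1.36 = 603.84, rounded up to the stated 604, or 302 per arm. The design difference is 5 points.

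**4. Illustration with no true app effect.** The inputs on motivation and quitting are assumed; the documents give none by motivation level.

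False difference = (share highly motivated, intervention − control) × (quit rate, high − moderate)

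With 70% vs 50% highly motivated and quit rates of 10% vs 4%:

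- Intervention: 0.7 × 10% + 0.3 × 4% = 8.2%
- Control: 0.5 × 10% + 0.5 × 4% = 7.0%
- Difference: 1.2 points, and 1.2 / 5 = 24% of the design difference

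If the shares are reversed, the result is −1.2 points.

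**5. Range.** 302 per arm, design effect 1.36 (effective 302 / 1.36 ≈ 222 per arm), 50% of controls highly motivated, two-sided 5% test of two proportions, **no adjustment**:

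| Highly motivated, intervention | Quit 3% vs 9%: false difference; type I error | Quit 3% vs 15%: false difference; type I error |
|---|---|---|
| 60% | 0.6 points; 5.8% | 1.2 points; 7.1% |
| 70% | 1.2 points; 8.0% | 2.4 points; 13.3% |
| 80% | 1.8 points; 11.6% | 3.6 points; 23.1% |

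**6. Would the planned model catch the case in step 4?**

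- Imbalance between arms: 0.20 / √(0.6 × 0.4 × 2 / 222) ≈ 4.3, so the baseline comparison would show it.
- Association of motivation with abstinence: of 604 patients, 60% (about 362) are highly motivated and 242 are not; pooled rate 0.6 × 10% + 0.4 × 4% = 7.6%. z = 0.06 / √(0.076 × 0.924 × (1/362 + 1/242)) ≈ 2.7, or 2.7 / √1.36 ≈ 2.3 after the design effect.
- The two-sided p<0.30 threshold is z = 1.04. The chance of passing is Φ(2.3 − 1.04) to Φ(2.7 − 1.04), about 90% to 95%.

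In this example Richmond would usually be adjusted for, but would be left out in roughly 5% to 10% of trials. Nothing comparable can be worked out for unmeasured traits.

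**The case against.** The strongest reply is that the traits most likely to differ are measured. Richmond, Fagerström, cigarettes per day and previous attempts are all recorded at recruitment, the groups are compared at baseline, and the model adjusts. **This stands in large part.** A reader might infer that a difference in motivation could not be told apart from the app's effect. The documents do not support that: step 6 shows that the planned rule would usually bring Richmond in. What survives is that entry is not guaranteed and that unmeasured differences are out of reach. The model also includes a dummy variable for baseline and 12-month measurements, but that does not name these scores or promise their inclusion.

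Other stronger readings also fail.

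- *The app arm would be favoured by about 1.2 points.* That figure is assumed and unadjusted. An app could as well attract less motivated smokers and bias against the intervention.
- *The recruiting staff themselves score the test that decides eligibility.* The Intervention section does not say who administers it.
- *The trial has no invitation log or rule for approaching patients.* A condensed article commonly leaves this to the full protocol, so its absence here is not counted as an error.
- *The article asserts that balance is achieved.* It states an aim, and it concedes in general terms that openness may bias the results. It does not, however, name recruitment after allocation as a route for that bias, and the aim extends to patients whom this design cannot balance by randomisation.

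Identical criteria in both arms, including a compatible smartphone, do narrow the scope for difference. They do not close it.

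**Conclusion.** The point holds as a risk and not as a demonstrated bias. The stated sequence allows the arms to differ at entry, and centre randomisation with centre-level stratification does not secure the patient balance that the Discussion looks to it for. Adjustment is a partial answer, weakened because baseline motivation and dependence must pass a p<0.30 screen.

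Neither direction nor size can be derived from the documents. Over the assumed scenarios the unadjusted false difference is 0.6 to 3.6 points, with a type I error of 5.8% to 23.1% against a nominal 5%. These figures rest on invented shares and quit rates, a simple two-proportion test in place of the planned survival model, and no adjustment. They show what could happen if the scores were left out, and much of each would disappear with Richmond in the model. This should be changed before recruitment, because records of who was invited cannot be reliably rebuilt afterwards.

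**What to change.** 1. **Statistical analysis:** include baseline Richmond score, Fagerström score and cigarettes per day in the primary model regardless of their p-values. All three are already collected, so this costs almost nothing.
2. **Intervention, visit 0:** complete consent, eligibility, Richmond and Fagerström in the same way in both arms before the centre's arm is discussed, as far as the ethics committee accepts for informed consent. The app is still first given at the appointment before D-Day, so no visit is added. Because the phone must be checked against the app's requirements, patients in both arms may learn that an app exists; a common script should handle this identically.
3. **Recruitment:** have centres invite eligible attenders consecutively and keep a short anonymised count of those eligible, invited and accepting, reported by arm. If the full protocol already provides for this, a sentence in the article is enough.
4. **Discussion:** state that centre randomisation does not ensure balance among patients recruited afterwards by unmasked staff, and name this as a limitation.

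The cost is a short log and a common visit-0 script at each centre. Recruiters still know their arm, so these steps reduce the risk and make it visible without removing it.

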#### Randomisation

The unit of randomisation will be the primary care centre, stratified according to urban/rural location and number of participating professionals to ensure comparability between the study groups, and then assigned 1:1 to the intervention or control group. Randomisation will use the Epidat 3.0 programme.

#### Blinding

Given the nature of the intervention, it is impossible to mask the participants or professionals to the study group assignments. However, data analysis will be blinded to any potential identifiers.

#### Patient inclusion criteria

a) Young adults aged 18 to 30 years who smoke at least 10 cigarettes per day; b) availability of the patient’s clinical history in the primary care centre; c) access to a smartphone device that meets the app requirements; d) access to an Internet data connection; and e) normal to high motivation to stop smoking on the Richmond test (score of 5 or higher).

#### Patient exclusion criteria

a) Addiction to other psychoactive substances; b) any baseline psychotic disease; c) use of a mobile device that does not comply with the app requirements; d) smokers with low motivation to stop smoking on the Richmond test (score of 4 or lower).

### Intervention

During the recruitment period, or until the required quota of patients is reached, the family doctor and/or primary care nurse will invite patients aged 18 to 30 years who smoke 10 or more cigarettes per day to participate in the study. If the patient is eligible for inclusion and agrees to participate, informed consent will be requested (Figure 1). After signing informed consent, the participant’s demographic data will be collected and the study questionnaire will be administered (Fageström & Richmond). During this visit (visit 0) smokers with moderate motivation to stop smoking (Richmond score of 5–6) will be invited to schedule a second appointment to attempt to increase their motivation. For highly motivated participants (Richmond score of 7–10) a “quit day” will be established within the following 15 days (D-Day), and they will be invited to schedule an appointment for the day before their D-Day.

**Figure 1 F1:**
[figure not shown]
Flowchart: randomisation of centres, and sampling and monitoring of patients.

At the pre-D-day appointment, smokers will begin their smoking cessation plan according to the clinical practice guidelines of the Catalan Health Institute. Participants randomized to the intervention group will receive the smartphone app, along with an explanation of how to use it to support their smoking cessation plan.

Follow-up and treatment for participants in both the intervention and control groups will follow the clinical practice guidelines. Participants who do not attend follow-up appointments will be telephoned, and will be considered relapsed as of that point.

#### Development of the mobile app

The app we are designing is included in what are called *serious games*, *half games* or *healthy games*. These types of apps have begun to gain recognition as powerful learning tools [8], since they offer those who play the opportunity to develop skills and strategies while they try to achieve the game’s objectives. In contrast to traditional educational methods, serious games are more focused on the views and participation of the learner, rather than the unidirectional guidance of the trainer. A serious game itself will not make smokers quit, but it will help to educate and guide those who wish to end their habit.

The three main objectives for app development are the following: (i) help the user record the progress of the smoking cessation plan; (ii) inform and educate the user about the problems of smoking and the improvements to be anticipated from smoking cessation; (iii) provide alternatives to the user for the times when he or she particularly wants to smoke; for example, a game might provide both entertainment (distraction) and subliminal or indirect messages that can help avoid the urge to smoke. The app will be adapted to the specific stages of the cessation process (typically 6 months duration), and will adjust to the progress of each participant.

To maximize the success of the intervention, a panel of smoking cessation experts, young smokers and ex-smokers, computer programmers, game developers, graphic designers and education experts will be involved at the different stages of the design and development of this app. Although we expect many ideas to emerge during the design process, we envision several options that will be offered to the participant to achieve these objectives:

(1) Information about tobacco: answers to frequently asked questions, advice, suggestions, definitions, illustrations and images.

(2) Private social network for study participants and staff: participants can communicate with each other to ask for help, share concerns, or offer help to others. The project staff will also post information about the process and offer helpful and supportive messages through this network.

(3) Minigame(s): games designed specifically to entertain and educate the participants.

(4) Progress registry: a visual representation of the evolution of the participant’s health progress through the treatment process.

